##### 1.8.2. Sample size calculation

The calculation of the sample size takes as its primary outcome treatment efficacy - the rate of complete elimination of MC at the final follow-up visit (60 days), as specified in a published clinical trial [7].

Based on this clinical trial, we expect a 20% cure rate in the control group and a 70% cure rate in one of the experimental treatment groups. To be able to detect these differences with a chi-squared test of two independent samples with a power of 80% at the 5% significance level, and with an estimated follow-up loss rate of 20%, there must be 20 patients per group.

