The present study will be conducted in a primary care setting, as the point of first contact within the National Health Service (NHS). The aim is to assess the efficacy of topical KOH treatment in 10% and 15% aqueous concentrations, versus a control (placebo) group in a pediatric clinic in a primary care center (PCC) in Lleida (Spain).

A randomized clinical trial (RCT) design has been chosen, with the objective of providing the maximum level of evidence. The treatment will be administered to three groups - one control and two treatment groups. This design will compare both treatment groups to the control group as well as compare the efficacy of the differences doses.

We hypothesize that the daily application of KOH treatment for MC is safe and affective in pediatric patients. Our bibliographic research has identified a paper [7] that estimates a 20% rate of successful resolution with placebo treatment and a 70% success rate with KOH treatment, with a mean treatment period of 54 days. Another study [8] without a control group and twice daily applications of 10% KOH reported 32 successful resolutions of 35 cases during a six month period.

This trial has been approved by the Ethical Committee of Clinical Trials of the IDIAP Jordi Gol (Primary Care Research Institute, Spain)

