In the case that the ANOVA cannot be used because a quantitative parameter does not fulfill the application criteria (non-normality/heteroscedasticity) the data will be transformed (logarithmic) from the original parameter, or a non-parametric analog test (Kruskal-Wallis) will be used. In all 2 × 2 comparisons (Group I, II vs. Placebo), the significance level will be adjusted for multiple comparisons.

The evolution of the quantitative efficacy parameters will also be assessed, by group, for the different time periods, using a repeated measures analysis.

The relationship between the baseline variables and the efficacy variables will be assessed at the end of the study, and in the case that an association is found, a multivariate analysis will be carried out to assess possible confounding factors of the group effect on adjusted efficacy: a multiple regression analysis will be used in the case of quantitative efficacy variables and a multinomial regression will be used in the case of qualitative variables.

The time from treatment to cure will be calculated as the difference between the date of first treatment and the disappearance of lesions or the end of the study (treatment initiation). Survival tables and the Kaplan-Meier statistic will be calculated to compare cure times between the different treatment groups. In the case that associations are found between efficacy variables and baseline conditions, a Cox proportional risk model will be adjusted.

Data analysis will be by ITT, by protocol and by safety sample.

In all cases a p-value below 0.05 will be considered significant.

Data will be analyzed using the statistical package "R": http://www.r-project.org.

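### The 20 per group was sized at an unadjusted 5% level, while the analysis section adjusts the level for the two KOH-versus-placebo comparisons; under Bonferroni, power per comparison is about 75%, not 80%

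*Protocol article*

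**What the plan says.** Four statements in the protocol article bear on this point.

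- **Sample size (1.8.2).** The assumption is that "we expect a 20% cure rate in the control group and a 70% cure rate in one of the experimental treatment groups". The test is a two-sample chi-squared test with "a power of 80% at the 5% significance level, and with an estimated follow-up loss rate of 20%, there must be 20 patients" in each group. Multiplicity is not mentioned.
- **Analysis (1.8.1).** "In all 2 × 2 comparisons (Group I, II vs. Placebo), the significance level will be adjusted for multiple comparisons". No method is named.
- **Analysis (1.8.1), later in the same section.** "In all cases a p-value below 0.05 will be considered significant".
- **Background.** The design is meant to "compare both treatment groups to the control group as well as compare the efficacy of the differences doses".

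The trial design summary caps randomization at 60 patients, which is 20 in each of three groups.

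**The concern.** The power statement and the analysis rule refer to different tests. The power statement is for one comparison at the full 5%. The analysis makes two comparisons with placebo at a stricter level. A stricter level with the same number of patients means less power, so the 80% may not describe the comparisons that will be reported.

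The blanket 0.05 sentence adds a second difficulty. Read literally, it cancels the adjustment. A reader cannot tell whether a KOH-versus-placebo p-value of, say, 0.04 would count as significant.

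Two things are at stake. A KOH group that works as assumed is more likely to miss significance than the plan states, and that result could be misread as coming from an adequately powered comparison. The level at which the main comparisons will be judged is also left open to two readings.

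**Working it through.** **Inputs from 1.8.2:** cure rates 0.20 and 0.70; power 80%; level 5%; loss 20%; 20 per group, so 20 × 0.8 = 16 evaluable.

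**Assumptions:** two-sided test (sidedness is not stated); equal groups; for the adjusted level, Bonferroni over the two placebo comparisons, 0.05 / 2 = 0.025 (the method is not stated).

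**Step 1. Reproduce the plan's figure.** The usual formula with pooled variance under the null and no continuity correction is

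n = [z(α/2)·√(2·p̄·(1−p̄)) + z(β)·√(p₁(1−p₁) + p₂(1−p₂))]² / (p₂ − p₁)²

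- p̄ = 0.45, so √(2 × 0.45 × 0.55) = √0.495 = 0.7036.
- √(0.16 + 0.21) = √0.37 = 0.6083.
- At α = 0.05: (1.960 × 0.7036 + 0.8416 × 0.6083)² / 0.25 = 14.3, so 15 evaluable.
- After loss: 15 / 0.8 = 18.75, so 19 per group.

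The stated 20 is reproduced to within one patient. With a continuity correction the answer would be 19 evaluable and 24 per group, so the plan's figure matches the uncorrected two-sided test at a full 5%, with no allowance for multiplicity.

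**Step 2. The same formula at 0.025.**

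- (2.241 × 0.7036 + 0.8416 × 0.6083)² / 0.25 = 17.5, so 18 evaluable.
- After loss: 18 / 0.8 = 22.5, so 23 per group, or 69 in total against the cap of 60.

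**Step 3. Power with 16 evaluable per group.**

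Power ≈ Φ{[0.5 × √16 − z(α/2) × 0.7036] / 0.6083}

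- α = 0.05: Φ[(2 − 1.379) / 0.6083] = Φ(1.02) = 84.6%.
- α = 0.025: Φ[(2 − 1.577) / 0.6083] = Φ(0.695) = 75.7%.

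Exact enumeration of both binomial outcomes for the uncorrected Pearson test gives 85.3% at 0.05 and 75.1% at 0.025.

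**Step 4. Other adjustments, 16 evaluable, placebo 20%, the KOH group in question 70%.**

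| Method | Power for that comparison |
|---|---|
| Bonferroni, 0.025 | 75.1% (exact) |
| Dunnett-type level, about 0.027 | 76.7% (normal approximation) |
| Holm, other KOH group cures 20% | 75.1% (exact) |
| Holm, other KOH group cures 50% | 76.4% (exact) |
| Holm, both KOH groups cure 70% | 81.2% (exact) |

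**Step 5. Would a closed test remove the problem?** Here the three-group chi-squared test at 5% comes first, and pairwise tests at 5% follow only if it is significant. Exact power for the 70% group depends on what the other KOH group does:

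| Other group's cure rate | 20% | 30% | 40% | 45% | 50% | 60% | 70% |
|---|---|---|---|---|---|---|---|
| Power | 82.5% | 79.4% | 77.4% | 77.3% | 77.7% | 80.0% | 82.7% |

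If all three groups have the same cure rate, the exact chance of a false positive is 4.3% at a 20% rate, 4.9% at 70% and 6.0% at 50%. The closed test therefore neither guarantees 80% power nor holds the error at 5% everywhere in groups this small.

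**The case against.** **The adjustment is unnamed, and the text is a condensed article.** This stands in part. The method may be set out in a full protocol or analysis plan that is not shown, and its absence alone is no fault. A reader might infer that 80% cannot be reached under any adjustment, but the documents do not support that. Holm gives 81.2% if both groups cure 70%, and Hochberg 82.8%. With the other group at 50% they fall to 76.4% and 77.5%, and section 1.8.2 assumes "a 70% cure rate in one of the experimental treatment groups", not in both. What the article does state, the level used for sizing and the intention to adjust, does not fit together whatever the method.

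**The gap is small and depends on 16 evaluable.** This stands. Under Bonferroni, exact power is 79.7% with 17 evaluable per group, 83.5% with 18 and 84.6% with 20. The ITT set needs only one treatment and one efficacy assessment, so it could hold more than 16 per group, depending on how missing day-60 outcomes are handled. But the 20% loss is the plan's own assumption, and its power claim has to be judged on it.

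**At least one KOH group would probably succeed.** True if both cure 70%: the chance that at least one is significant at 0.025 is about 88%. That is a different quantity from the power of the single comparison in 1.8.2, and the Background promises both comparisons with placebo.

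**The dose comparison.** A reader might infer that the trial is wrongly sized because 10% against 15% is not powered. That does not follow. Comparing efficacy across the three groups is a secondary objective, and a sample size need not be built on it. It is enough to say what the 80% covers.

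**Conclusion.** The mismatch is real as written: 1.8.2 sizes at an unadjusted 5%, 1.8.1 adjusts the level for the same comparisons, and 1.8.1 then states a uniform 0.05 threshold. The 20 per group is not an arithmetic error; it is correct for the inputs it uses.

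Assuming Bonferroni, a two-sided uncorrected chi-squared test and the plan's 20% loss, power per KOH-versus-placebo comparison is about 75%. That is about 5 points below the stated 80%, and about 10 below the 85% that the same 16 per group would give at 0.05. A Dunnett-type level also falls short. Holm reaches 80% only when the other KOH group also does well.

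The shortfall does not raise the false-positive risk and does not invalidate the design. It should be fixed; it is not a condition for going ahead.

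**What to change.** **In 1.8.1:** name the adjustment for the two KOH-versus-placebo comparisons, and make the blanket 0.05 sentence subject to it, for example: *p below 0.05 is considered significant, except in the comparisons of each KOH group with placebo, where the adjusted level applies.*

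**In 1.8.2:** restate the power at the named level. Under Bonferroni the sentence could read: *with 20 patients per group and 20% loss (16 evaluable), power to detect 70% against 20% is about 75% for each KOH group versus placebo at the two-sided 0.025 level.* Add that this figure does not cover the comparison of 10% with 15%. If another method is chosen, give its power together with the cure rate assumed for the other KOH group.

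Do not state that a closed test restores 80%; its power runs from about 77% to 83% depending on the other group.

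**Cost:** wording in two sections and no extra patients. The price is a slightly less favourable stated power. Keeping 80% under Bonferroni would instead take 23 per group, 9 patients above the cap of 60.

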#### 1.9. Quality control and quality assurance

In order to ensure the Quality of the data the delegated organization will:

• Perform regular monitoring according to ICH GCP guidelines. Data will be evaluated for compliance with the protocol and accuracy in relation to source documents. Monitors will verify that the clinical trial is conducted and data are generated, documented and reported in compliance with the protocol and the applicable and local regulatory requirements.

• Provide instructions and training to the sites involved in the trial.

• Review the CRF data.

• Detail of any other steps taken to ensure research quality.

## Discussion

Currently, there is no satisfactory treatment for the rapid and non-invasive treatment of MC lesions, so pediatricians normally allow the infection to run its course, with duration of between six months and a year. This situation imposes considerable limitations on the patient's lifestyle, especially regarding the use of public facilities (gyms, pools) due to the elevated infectivity of the virus, and psychological and social effects especially in children.

KOH may be a good therapeutic alternative if it is effective, easy to apply, can be self-administered, has minimal side effects and is inexpensive. The few published studies on the subject do not provide definitive evidence about KOH as a treatment for MC, given that these studies have not compared different solution concentrations and placebo.

The results of our clinical trial will make it possible to definitively assess all these aspects of this treatment. Furthermore, conducting the study in a pediatric primary care setting, the gateway to the Spanish national health system, makes it possible to evaluate the utility of the treatment at the primary care level, addressing the majority of cases that could benefit from this treatment while also decreasing referrals to hospital specialists.
